### **6.1.5 Baseline measurements and sample collection**

Baseline measurements and venous blood collection (10 mL) will be conducted 4 weeks after enrollment and 3 days after the final dose of the PQ and PL drug regime. During the baseline visits the PNGIMR field study team will conduct the following tasks:

- Assess the child's health status including
  - body temperature
  - symptoms of malaria or other infections
  - spleen size
- Interview the parent and/or guardian and record:
  - history of child's bed net use in 2 weeks prior,
  - child's history of febrile illness/malaria in 2 weeks prior,
  - child's history of malaria treatment in 2 weeks prior (except treatments given by study),
- Check the child's health records booklet for recent health center visits and record applicable information,
- Collect 10 mL venous blood sample,
  - Prepare thin and thick blood smears,
  - Prepare filter paper blood spot
  - Archive samples for laboratory analyses (PCR-typing plus auxiliary immunology),

If the participant has symptoms of clinical malaria he/she will be diagnosed in the field using a rapid diagnostic test (RDT) for malaria and HemoCue® for Hb concentration. For children excluded from undertaking RDT tests, blood smears will be read overnight for malaria diagnosis. Upon positive RDT, or positive blood smear or in the case of moderate-to-severe anemia (Hb <8.0 g/dL) the study team will initiate treatment with Coartem according to national treatment guidelines.

#### **6.1.5.1 Participant Database and Study Visit Activities**

After enrollment, the child's baseline information will be entered into a participant's database that will provide scheduling information for the surveillance activities every 2 weeks. The participants'

database will be updated every 2 weeks to reflect the status of the cohort through indicators that distinguish children under active follow-up versus those censored from follow-up for various reasons. The participant database will serve to schedule active surveillance visits for the study children. Using the baseline fixed information on the demographics of the participant and the dynamic information on the follow-up status of the child, active surveillance forms will be pre-printed from the participants database with study identification numbers, family information, and measurements and information to be collected during the study visit.

### **6.1.6 Active Surveillance**

Following the collection of the 10 mL venous blood sample the study team will contact each participating child every 2 weeks and conduct a brief clinical evaluation of each child during a clinic held at the participant's school.

The study team will specifically perform the following tasks:

- Record axillary body temperature of the child,
- Assess the child for symptoms of malaria infection,
- Determine if the child is suffering from symptomatic malaria (or clinical signs and symptoms of anemia),
- Check the fingers of the child for redness or signs of irritation from lancet finger punctures.
- Record information relating to:
  - history of bed net use for the study participant since the previous visit,
  - participant's history of illness since previous visit,
  - history of malaria treatment for the study participant since previous visit,
- Check the child's health records booklet for recent health center visits and record applicable information,
- Inform the child's teacher and school administration of the next follow-up visit and the reasons for the tasks to be performed.

If the participant is judged to be suffering from malaria illness at the time of the morbidity surveillance visit, finger prick blood samples will be collected for determination of parasitaemia and Hb levels. The presence of malarial parasites will be diagnosed in the field using RDT. For children excluded from undertaking RDT tests, blood smears will be read overnight for malaria diagnosis. Upon positive RDT or positive blood smear or in the case of moderate-to-severe anemia (Hb <8.0 g/dL) the study team will initiate treatment as per national standard treatment guidelines.

In the first 12 weeks of follow-up, a 250 µL finger prick blood sample will be collected at 2 weekly morbidity surveillance visits. Thereafter a finger prick sample will be collected every 4 weeks only.

The blood samples will be used to produce blood smears for assessing blood-stage malaria infection, type of *Plasmodium* parasite(s), and level of parasitaemia. A portion of this sample will be collected in a microtainer for further analysis (i.e., PCR/LDR-based diagnosis of malaria infection and for immunological studies). A few drops of blood will be collected on a filter paper for detection of gametocytes.

In total the team will conduct 16 follow-up visits that will include 11 finger prick blood sampling time points.

All enrollment, baseline and active follow-up visits will be done by 2 mobile teams in the study communities. A 3rd team will help during the intensive DOT pre-treatment phase of the study. Each school will be visited on the same days over a 2-week period. Symptomatic children detected during the study clinics will be referred to the Albinama health centre or Maprik Hospital.

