## 4 STUDY DESIGN

In this study 500-600 children aged 5-10 years will be screened, enrolled and randomized to 2 arms of a longitudinal cohort study. The randomized arms will comprise:

- 250-300 children pre-treated with 3 days Chloroquine (CQ), 4 weeks Primaquine (PQ) and 3 days Coartem (CO)
- 250-300 children pre-treated with 3 days Chloroquine (CQ), 4 weeks Placebo (PL) and 3 days Coartem (CO)

At enrolment all eligible children aged 5-10 years in the study area will be screened for Glucose-6-Phosphate Dehydrogenase deficiency (G-6-PD) and the presence of severe anaemia or malnutrition. Children with less than 60% G-6-PD activity, haemoglobin <5g/dl or severe malnutrition (weight-for-age nutritional Z score [WAZ] <60th percentile) will be excluded from the study. All other children will be randomized to the two treatment arms of the study.

Drug treatment will commence at enrolment. All children will receive CQ on days 1-3. Children will also receive either PQ (0.5 mg/kg) or placebo on days 1-5, 8-12, 15-19 and 22-26 (i.e. Monday to Friday for 4 weeks). During the third week of drug treatment all children will receive CO on days 15-17 (according to national treatment guidelines). Children will be actively monitored for side effects including measurement of haemoglobin levels at days 1, 8, 15 and 22.

Following completion of treatment, children will undergo a clinical examination and a 10 mL venous blood sample will be collected on day 29 (i.e. 26 days after their last dose of CQ, 12 days after their last dose of CO and 3 days after their last dose of PQ or PL).

Subsequently, all enrolled children will be followed using 2-weekly active and continuous passive case detection at a local health centre for 8 months (Week 2-32). Active follow-up consists of morbidity surveillance visits to monitor clinical malaria illness not reported to a health facility, as well as blood sampling for the detection of asymptomatic malaria. These visits will include collection of a medical history of the preceding 2 weeks to determine incidence of malarial infections and bed net usage, a physical examination, measurement of axillary temperature. A 250µl finger prick blood sample will be collected every 2 weeks for the first 12 weeks and 4 weekly thereafter, i.e. weeks 2, 4, 6, 8, 10, 12, 16, 20, 24, 28 and 32.

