All blood samples will be assessed for the presence, type, and number of malarial infections (by light microscopy and PCR) and Hb levels. The 10 mL venous blood samples will also be used for the assessment of humoral and cellular immune responses to *Plasmodium* infections (Aim 2). DNA

extracted from venous blood samples and the finger-prick blood samples collected during follow-up will be assessed in molecular parasitology studies (Aim 1).

During the entire study period, a passive case detection system will be maintained at the local Health Centre. Every participating child that presents at the health centre with a febrile illness will be clinically assessed and have a finger prick blood sample taken for determination of malaria infections by a Rapid Diagnostic Test (RDT), two blood slides for microscopy confirmation and HemoCue® for Hb concentration. In accordance with the new national treatment guidelines, only children with a positive RDT will receive Coartem treatment from the attending field Nurse. All the data collected will be recorded in the morbidity forms and the health book of each participating child to be reviewed by the study clinician.

Over the 9-month study duration, each participant will have 38 contacts with the study team (1 for enrolment/screening, 20 for supervision of drug administration, 1 baseline time-points (after drug treatment), 16 active follow-up visits) and will be asked to contribute one 10 mL venous blood sample at the baseline visit and 12 finger prick blood samples (250µL) (see Study Schedule Diagram, Appendix I.) Additional finger prick blood samples may be collected at the time of febrile illness during morbidity follow-ups and passive case detection.

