**Follow-up and Morbidity Surveillance**

Finger prick blood samples of approximately 200 -250 µL will be collected every two weeks for the first 12 weeks and 4 weekly thereafter from each child participating in the study. Additional samples will be taken from symptomatic individuals at both active and passive morbidity surveillance visits. Blood samples will be obtained by the finger-stick method. This sample will provide adequate blood for the preparation of thin/thick blood smears to detect the presence of malaria parasites, type of malaria parasites, and level of parasitaemia. At baseline and the final visit, part of the sample will also be used to determine Hb concentration. The samples collected in microtainers will be processed into cell pellet (for DNA preparation, PCR/LDR-based diagnosis of malaria parasites and Duffy genotyping) and plasma (for immunological investigations).

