## 8 ASSESSMENT OF OUTCOME MEASURES

### 8.1 Specification of the Appropriate Outcome Measures

#### 8.1.1 Primary Outcome Measures

- Time-to-first *P. vivax* and *P. falciparum* infections by LM and PCR in the 32 week follow-up period. (Aim 1)
- Incidence of first or only *P. vivax* and *P. falciparum* infection by LM and PCR during the 32 weeks of follow-up. (Aim 1)
- Incidence of clinical *P. falciparum* and *P. vivax* episodes during the 32 weeks of follow-up. (Aim 1 & 2)
- Incidence of first or only clinical *P. falciparum* and *P. vivax* episode during the 32 weeks of follow-up. (Aim 1 & 2)

Clinical *P. falciparum* and *P. vivax* malaria is defined as an axillary temperature  $\geq 37.5^{\circ}$  (or a history of fever lasting more than 2 days in duration) together with concurrent *P. falciparum* and/or *P. vivax* parasitaemia.

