#### 11.1.2 Primary Outcome Measures

##### **11.1.2.1 Incidence of clinical *P. falciparum* or *P. vivax* episodes during the 32 weeks of follow-up**

The comparison of the incidence of clinical *P. falciparum* and *P. vivax* episodes between the 2 study arms is a primary objective of the study and will be evaluated by assessing differences in both the incidence of *P. falciparum* *P. vivax* episodes over 32 weeks of follow-up and the incidence of first or only *P. falciparum* / *P. vivax* episodes

Children will be considered 'at risk' until they reached the endpoint of interest, withdrew, were lost to follow-up or completed the study. For clinical and molecular endpoints children were censored on the last day before the first of two consecutively missed active follow-up visits

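### After week 12 a child without symptoms who misses one sampling clinic goes 8 weeks between blood samples while still counted at risk, although the team is back at the school 2 weeks later

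*Protocol*

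**What the plan says.** Section 4 lists the routine finger-prick samples: "i.e. weeks 2, 4, 6, 8, 10, 12, 16, 20, 24, 28 and 32". Section 6.1.6 gives the same pattern, fortnightly to week 12 and then: "Thereafter a finger prick sample will be collected every 4 weeks only". Contact with the children does not thin out. Every 2 weeks throughout follow-up the team is to "conduct a brief clinical evaluation of each child during a clinic held at the participant's school". The totals agree with this: "In total the team will conduct 16 follow-up visits that will include 11 finger prick blood sampling time points".

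The only further blood described is for illness. Section 6.2.2.1 says: "Additional samples will be taken from symptomatic individuals at both active and passive morbidity surveillance visits". Sections 4 and 6.1.6 say much the same.

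Section 8.1.1 makes time to first infection, and incidence of first or only infection, primary outcomes for *P. vivax* and *P. falciparum*. The first of these is worded as "infections by LM and PCR in the 32 week follow-up period". Section 11.1.2.1 sets the rule for missed visits, for clinical and molecular endpoints alike: "children were censored on the last day before the first of two consecutively missed active follow-up visits".

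**The concern.** The infection endpoints are seen almost entirely through the scheduled samples. From week 14 on, every second clinic takes no routine blood. A child absent at week 16 who returns at week 18 is examined, is not bled unless ill, and is next sampled at week 20.

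The censoring rule counts missed visits, not missed samples. One absence does not remove the child from the risk set, so the unsampled weeks count as time at risk without infection unless a later sample is positive. An infection that starts and clears inside the gap is never counted. One already present at the missed visit, and persisting, is dated 4 weeks later than it would have been.

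Symptom-driven sampling fills little of this gap for *P. vivax*. Section 2.1 describes almost complete clinical immunity to *P. vivax* by age 6 in the earlier Madang study. The model for acquisition and loss of infections (section 3) also loses observations in the period where they are already sparsest.

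**Working it through.** **Schedule check.** Visits: 32/2 = 16. Samples: 12/2 + (32 − 12)/4 = 6 + 5 = 11. Both match section 6.1.6.

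**Gap after one missed sample, and with a make-up sample 2 weeks later**

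| Missed week | Samples either side | Gap now | Longest gap with make-up |
|---|---|---|---|
| 2–10 | 2 weeks each side | 4 weeks | no change proposed |
| 12 | 10 and 16 | 6 weeks | 4 weeks (10 to 14) |
| 16 | 12 and 20 | 8 weeks | 6 weeks (12 to 18) |
| 20, 24, 28 | 4 weeks each side | 8 weeks | 6 weeks |
| 32 | 28, none after | no later sample | cannot be replaced |

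A persistent infection acquired between weeks 12 and 16 in a child absent at week 16 is found at week 20, not week 16: 4 weeks later. With a sample at week 18 it is 2 weeks later.

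**How many children.** The protocol gives no absence rate. I assume q = 10% or 20% per visit, independent between visits. The share missing at least one of the five samples at weeks 12, 16, 20, 24 and 28 is 1 − (1 − q)^5: 41% or 67%. In 500 children the missed samples number 5 × q × 500 = 250 or 500. Those recoverable at the next visit are 250 × 0.9 = 225 or 500 × 0.8 = 400.

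**How much of the endpoint lies after week 12.** With exponential times and the medians in section 11.2.1, the control-arm share still uninfected at day 84 is 0.5^(84/median). This is 34% for PCR (54 days) and 61% for light microscopy, LM (118 days).

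**Effect on observed first infections.** I simulated infections arriving at rate ln2/median, with a hazard ratio of 0.66 (LM) or 0.70 (PCR). They were detectable only at samples actually taken, with no censoring for treatment or withdrawal. Mean patency of 2–4 weeks is assumed. For LM the medians are 118 days and 236 days, the latter if bednets halve the rate.

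| Measure | 10% absence | 20% absence |
|---|---|---|
| LM, make-up at weeks 14, 18, 22, 26, 30 | +2.0 to 3.4% | +4.2 to 6.9% |
| PCR, median 54 days, make-up at weeks 18–30 | +1.0 to 1.6% | +2.4 to 4.0% |
| Either, infections persist | under +1% | under +1% |

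Adding week 14 leaves the PCR gain at about 1–4% over both absence rates.

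**Dating and detection** (control arm, PCR median 54 days, infections starting after week 12). For persistent infections, the mean delay from onset to detection is 2.1 weeks with no absence. At 10% absence it is 2.5 weeks, or 2.3 with make-up; at 20% it is 3.0, or 2.4 with make-up. If infections last 4 weeks on average, 18% of children first infected after week 12 never test positive even with no absence. At 10% absence this is 22%, or 20% with make-up; at 20% it is 26%, or 22% with make-up.

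**Power.** Schoenfeld: power = Φ(|ln HR| × √D / 2 − 1.96), with D events, 200 per arm, and two-sided 5% assumed because the protocol states no alpha.
- PCR, 54 days, persistent, 20% absence: D = 359 with or without make-up, 92.2% both ways.
- PCR, 54 days, 4-week infections, 20% absence: D = 304 gives 87.5%; with make-up D = 311 gives 88.2%.
- LM, 236 days, 2-week infections, 20% absence (largest gain): 101 events at 250 per arm scale to 101 × 200/250 = 80.8, giving 46.3%. With the 6.9% gain, 80.8 × 1.069 = 86.4, giving 48.8%. The difference is 2.5 points.

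**The case against.** Nothing here is contradictory. The schedule is the same wherever it appears, the counts reproduce, and thinning the samples after week 12 is a deliberate choice. The word "only" in section 6.1.6 most naturally contrasts 4-weekly with fortnightly sampling, so a reader should not infer that the protocol forbids a late sample. Section 13 leaves field tasks to standard operating procedures that are not shown, and one of them may already cover absentees. Section 6.1.5.1 describes visit forms pre-printed from a database updated every 2 weeks, which could carry a missed sample forward. All of that stands. But the sampling weeks are fixed in the protocol, and as written they give no make-up sample.

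The size of the effect rests on absence and patency rates that the protocol does not give. Section 11.2.1 literally assumes a 50% decrease in time to infection, which would put the LM median at 59 days rather than 236. The LM gain is then smaller, 1.2–3.8% with make-up at weeks 18–30. This also stands, and is why the result is given as a range.

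The planned acquisition and loss model already allows for imperfect detection. That helps the model but does not restore missing observations, and the first-infection analyses have no such allowance.

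A reader might also infer that the gap biases the treatment comparison. The protocol does not support that. Placebo keeps families and staff blinded (section 6.1.4) and the visit schedule is the same in both arms, so absence alone is not expected to favour either.

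**Conclusion.** The point holds as a small, inexpensive improvement to the data for the primary infection outcomes. As written, one absence at week 16, 20, 24 or 28 leaves a child without symptoms 8 weeks between samples and still at risk; absence at week 12 leaves 6 weeks. A make-up sample shortens the 8-week gap to 6 and the added dating delay from 4 weeks to 2. It does not remove either.

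Under the stated assumptions the gain is about 2–3% more observed LM first infections at 10% absence, 4–7% at 20%, about 1–4% for PCR, and under 1% if infections persist. Power changes by about 0–2.5 points.

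It would be wrong to conclude that the trial's power depends on this, or that 4-weekly sampling is itself an error. It would also be wrong to say that every absent child is affected: a child judged to have malaria illness is sampled at any visit. Nor does the problem begin strictly after week 12, since a missed week 12 sample already leaves a longer gap.

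**What to change.** In sections 4 and 6.1.6, replace the post-week-12 rule with: thereafter every 4 weeks; a child absent at a scheduled sampling visit from week 12 to week 28 gives that sample at the next fortnightly visit, if attended (week 14, 18, 22, 26 or 30). Record the actual sampling date and use it in the infection analyses.

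This fits the existing censoring rule. A child who also misses the make-up visit has missed two visits in a row and is censored from before the first, so the new sample reaches the children whom the rule keeps at risk.

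The cost is one sentence. The visits already exist, the pre-printed forms can flag a sample owed, and no child exceeds the planned number of finger pricks. The downside is slightly less uniform sampling dates. A missed week 32 sample remains lost.

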### **6.1.7 Passive case detection**

The schools in the study are within less than 10km (i.e. up to 3 hours walk) of Albinama health centre. The health centre has both in-patient facilities and is staffed with a health extension officer and several nurses and community health workers. The health centre staff routinely assesses patients for malaria and upper respiratory tract infections (the 2 most common reasons for seeking treatment). As at all other PNG health centres, attendance and admittance log books are kept.

The study team will coordinate with the health centre nursing staff for the collection of illness and treatment histories of study participants on special Health Centre Surveillance Forms. The health centre staff will be requested to screen incoming patients who are between 5-10 years of age in order to determine if they are study participants. If the health centre staff identifies the incoming patient as a study participant, the nursing staff will refer the patient to a health centre based study nurse. The nurse will take detailed history, fill in the Health Centre Surveillance form, do a finger prick blood sample to obtain blood smears and for determination of infecting malaria species, measure Hb and confirm the presumptive diagnosis using RDT, unless the child has received malaria treatment in the previous 2 week period. For children excluded from undertaking RDT tests, blood smears will be read overnight for malaria diagnosis. In the case of a positive RDT or positive blood smear or, a Hb <8.0g/dL, the child will be treated with a locally available appropriate antimalarial treatment and iron supplementation by the study nurse.

Results of RDT and Hb measurement will be passed onto health centre staff. For children with negative RDT the health centre staff will be advised to refine the diagnosis for other febrile illnesses and treat accordingly.

All health centre visits will be recorded in the child's health booklet, which will be cross-checked at the active morbidity surveillance time points.

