## Protocol Summary

**Title:** Host and parasites factors contributing to risk of *Plasmodium* re-infection and morbidity in elementary school children in Maprik, East Sepik Province

**Population:** 500 children 5-10 years of age, who are residents of malaria-endemic villages near Maprik in the East Sepik Province, Papua New Guinea (PNG).

**Number of Sites:** 1 field site (4-8 elementary schools, Maprik District, PNG), 4 laboratory sites (Goroka & Madang PNG, Melbourne, Barcelona)

**Study Duration:** 9 months

**Subject Duration:** 9 months

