**The secondary objectives will be assessed by:**

- determining the rates of clinical episodes of *P. falciparum* in children that have received pre-treatment with either, blood-stage drugs alone (chloroquine/coartem plus placebo), or blood-stage plus liver-stage drugs (chloroquine/coartem plus primaquine) through two 6-month follow-up periods.
- Determining the presence of gametocytes using light microscopy and reverse-transcriptase PCR from filter paper blood spot and comparing the prevalence of both asexual and sexual parasites in all blood samples collected.
- studying the associations between increased age and incidence of malarial infections and disease in both treatment arms.

**Aim 2: Measure naturally acquired immune responses to both *P. falciparum* and *P. vivax* and investigate their association with subsequent risk of *P. falciparum* and *P. vivax* infection and disease in children 5-10 years of age.**

This study aims to ascertain the extent of naturally acquired cellular and humoral immune responses to a range of *P. falciparum* and *P. vivax* blood pre-erythrocyte stage antigens in children 5-10 years age and determine their possible associations with protection against *P. falciparum* and *P. vivax* infections and disease. For that purpose we will measure immune responses in venous samples collected from all children after drug treatment and relate different immune measurements to risk of infection and disease during the 8 months of follow-up.

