## 5 STUDY POPULATION

### 5.1 Selection of the Study Population

Data from both active and passive morbidity surveillance in the Wosera area show that the incidence of both *P. falciparum* and *P. vivax* malaria is greatest in the 1- to 5-year old age group but remains a significant burden in the 5-10 year old age bracket, during which time the children are acquiring clinical immunity, particularly to episodes of *P. falciparum*. A recent study in Madang (10) showed that in an area of hyperendemic transmission children of the 6-12 year age group had already acquired a high degree of clinical immunity to *P. vivax* but were still experiencing significant numbers of *P. falciparum* clinical episodes despite similar incidence of new blood stage infections.

This study will thus be done in children 5-10 years of age ( $\pm 3$  months). This age group is selected because:

- a) Children in this age group have acquired a sufficient degree of immunity to exert a significant amount of control on parasite but are still at significant risk of symptomatic illness with at least *P. falciparum*.
- b) An earlier study in a similar age group (5-12) in Madang showed that this age group is thus ideal for determination of immunological correlates of natural acquisition of immunity to *P. falciparum*. A 2nd study in the same age group is now required will allow findings from a similar study north of Madang to be confirmed in a children in a different region of PNG.
- c) This will allow for an extension of a previous liver-stage/blood-stage treatment to re-infection study into slightly older children. Together these studies will cover the entire age range (1-10 yrs) from non-immune to highly clinically immune.
- d) The lower number of clinical episodes in this age group will allow to study the dynamics of acquisition and loss of individual *P. falciparum* and *P. vivax* infections in semi-immune individual in the absences of frequent drug treatment.

The study will enroll 500-600 children with approximately the same numbers of male and females. All study participants will be ethnic Melanesian.

Children will be recruited from elementary schools in the vicinity of the Albimana health center (see Figure 3 in Section 5.2). Albimana is an ideal study location. It has a similar malaria prevalence rate as the neighboring Ilaita area and is accessible by road all year round.

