**Figure 3. Study location – The Ilahita/Albinama/Wosera area, East Sepik Province, Papua New Guinea**

## 5.2 Inclusion/Exclusion Criteria

Children are eligible for participation in this study if they fulfill the following criteria:

- aged 5-10 years ( $\pm 3$  months in children without known date of birth),

- permanent residents of the area,
- absence of history of hypersensitivity reactions to the pre-treatment drugs.

At enrollment and upon informed consent, all eligible participants (see Section 5.1 above for criteria) will be screened for the following exclusion criteria:

- chronic illness,
- severe malnutrition (weight-for-age nutritional Z score [WAZ] <60th percentile)
- severe anemia (Hb <5 g/dL),
- G-6-PD deficiency (<60% G-6-PD activity)
- permanent disability, which prevents or impedes study participation.

Any 1 or more of the criteria is sufficient to exclude study participation.

Children with moderate to severe anemia (i.e. Hb 5 - 8 g/dL) can be enrolled, but will be treated according to national guidelines with a full course of antimalarials, albendazole and 4 weeks of daily oral iron supplementation. Children with severe malnutrition and severe anaemia (Hb < 5.0g/dL) will be referred to the local health centre for treatment according to national treatment guidelines.

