#### **6.1.9.1 Health Record Booklets**

All participants in PNGIMR studies are recommended to purchase and carry a health records booklet when seeking medical care at health centers. The health records booklet provides information as to the immunizations, illnesses, and treatments an individual has had. Additionally, the health records booklets for participants in collaborative research studies are marked with a brightly colored sticker. The sticker alerts health care providers at the health centers that the individual is participating in a research study.

Each of the health records booklets of study participants will be marked with a sticker denoting participation in this study. In the event a participant of the study does not have a health records booklet, a booklet will be provided at no cost to the parents and/or guardians of the participant and marked with a unique sticker showing study participation. Ilahita health center and surrounding Aid Post staff will be informed of the study and the type of sticker denoting participation.

The field study team will review each participant's health records booklet at the regularly scheduled study visits, record all health care visits on the Study Team Visit Form, and coordinate with the health center at least every 2 weeks to ensure that extracts of the Health Center Surveillance Forms have been obtained.

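### Health-centre staff are asked to look for participants only among patients aged 5-10, the entry bracket, so some clinical episodes in children who pass that age during the 9 months may be missed

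*Protocol*

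**What the plan says.** Section 6.1.7 describes how participants are found at the health centre: "The health centre staff will be requested to screen incoming patients who are between 5-10 years of age". The stated purpose is to establish whether the patient is a participant. A child identified in this way is passed to the study nurse, who takes the history, the finger-prick sample and the smears.

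The bracket matches the entry criterion. Section 5.1 states: "This study will thus be done in children 5-10 years of age", and section 5.2 allows a tolerance of 3 "months in children without known date of birth". The Protocol Summary gives "Subject Duration: 9 months", and section 4 says that "all enrolled children will be followed using 2-weekly active and continuous passive case detection at a local health centre for 8 months".

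Other sections set no age limit. Section 4 says: "Every participating child that presents at the health centre with a febrile illness will be clinically assessed". Section 6.1.8.3 has all participants with presumptive malaria referred to the study nurse. Section 7.6 does not list reaching an age limit as a reason for discontinuation.

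Section 6.1.9.1 puts a sticker on each participant's health booklet, and then says: "Ilahita health center and surrounding Aid Post staff will be informed of the study and the type of sticker denoting participation". Sections 6.1.7 and 6.1.8.3 place the passive-detection centre and its study nurse at Albinama. Section 5.1 treats the Ilahita area (spelled differently there) as a neighbouring area.

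One secondary objective under Aim 1 is assessed by "studying the associations between increased age and incidence of malarial infections and disease in both treatment arms".

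**The concern.** An entry criterion is being reused as a case-finding rule during follow-up, when the children are older. A child near the top of the bracket at enrolment may be outside it for part of follow-up. A child admitted under the 3-month tolerance below age 5 may start outside it.

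If such a child attends the health centre and is not recognised, the study nurse takes no smear or sample. Under sections 8.1.1 and 11.1.1 a clinical episode needs concurrent parasitaemia, by smear or PCR, or a density above a threshold. An unsampled visit therefore cannot be counted as a confirmed episode. The child's risk time still counts: section 11.1.2.1 ends it at the endpoint, withdrawal, loss to follow-up, completion or two consecutive missed active visits. A missed health-centre referral is none of these.

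Such a loss would fall mainly on the oldest children. It would lower their recorded clinical incidence, which is also the direction expected from acquired immunity. Randomisation does not protect a comparison between ages.

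**Working it through.** The protocol gives no figure on this point, so there is nothing to reproduce. The check bounds the exposed group by ageing arithmetic, then sets the safeguards against it.

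**Inputs from the protocol**
- Screen at the health centre: 5-10 years (6.1.7). Entry: 5-10 years (5.1, 5.2).
- Timing: 4 weeks of treatment, then 32 weeks of follow-up (section 4, Table 3). Follow-up thus runs from week 4 to week 36 after enrolment, with midpoint (4 + 36)/2 = week 20.
- Sample size: 500-600 children (section 4).

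**Assumptions, not in the protocol**
- Entry ages uniform over 6 years (5 to under 11) or 5 years (5 to exactly 10).
- The bracket is read the same way at entry and at the clinic.
- 30%, 50% or 80% of episodes are found only through passive detection.
- 52.18 weeks per year.

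**Children passing the upper limit by week 36** = (36/52.18)/span = 0.690/span
- 6-year span: 0.690/6 = 11.5%, about 58 of 500 or 69 of 600.
- 5-year span: 0.690/5 = 13.8%, about 69 of 500 or 83 of 600.

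**Follow-up time beyond the limit** = (20/52.18)/span = 0.383/span
- 6-year span: 0.383/6 = 6.4%.
- 5-year span: 0.383/5 = 7.7%.
- Within the oldest one-year entry band: 69% of children and 38% of follow-up time.

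**Cut in recorded clinical incidence, oldest band** = 0.383 × passive share × share of over-age visits missed

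| Passive share | All missed | Half missed | One tenth missed |
|---|---|---|---|
| 30% | 11% | 6% | 1% |
| 50% | 19% | 10% | 2% |
| 80% | 31% | 15% | 3% |

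Over the whole cohort, with every over-age visit missed, the cut runs from 0.0639 × 0.30 = 1.9% to 0.0767 × 0.80 = 6.1%.

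**A reading with no loss at the upper limit.** Suppose entry stops at exactly 10.0 and clinic staff count completed years. With the full tolerance, the oldest child finishes at 10.0 + 0.25 + 0.69 = 10.94 years, is still a 10-year-old, and nobody ages out.

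**What the safeguards recover**
- *Sticker and booklet marking (6.1.3, 6.1.9.1).* These work at any age, and if staff act on them the loss is zero. But the staff to be briefed on the sticker are named as Ilahita's, not Albinama's.
- *Referral of all participants (6.1.8.3).* This presupposes that staff know the child is a participant. Section 6.1.7 is where the protocol says how they find out.
- *On-site nurse (6.1.9).* Under 6.1.7 the nurse receives children whom health-centre staff have already identified.
- *Booklet cross-check and record extraction (6.1.6, 6.1.7, 6.1.9.1).* These recover the visit and the treatment, but not a study smear or density.
- *Two-weekly active visits (6.1.6).* Children ill at the visit are sampled. An episode treated at the health centre in between may have cleared, and routine finger pricks become 4-weekly after week 12.

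**The case against.** The strongest reply is that section 6.1.7 describes an aid to case finding, while sections 4 and 6.1.8.3 state the rule. Section 6.1.7 does not say that a participant outside 5-10 is turned away, and referral depends on being recognised as a participant. Every booklet carries a study identifier and a sticker, a study nurse is present in all out-patient hours, and the team obtains extracts from the health centre at least every 2 weeks. The Ilahita reference may be only a misplaced name, since Albinama staff work alongside the study nurse. An exact birthday cut-off also cannot be applied to children whose birth date is unknown.

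Most of this stands. A reader might infer that children who pass the limit drop out of passive detection and that incidence in the oldest is artificially cut. The protocol does not support that: no section ends passive detection at a birthday, and several routes operate regardless of age. Nor does it support a claim of bias between the arms, because the arms are randomised and blinded and any loss should fall on both alike.

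What remains is narrower. The only step that says how staff find participants is tied to the entry ages. The backup is briefed at a differently named centre. The other checks cannot supply the parasitology that an episode requires.

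**Conclusion.** The point holds as a gap in procedure that may lose some clinical episodes in the oldest children. Section 6.1.7 is narrower than the coverage intended in sections 4 and 6.1.8.3. Under uniform entry ages and a consistent reading of the bracket, 11-14% of children and 6-8% of follow-up time lie past the limit.

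The size of the loss is unknown and may be zero. The 11-31% cut in the oldest band is an upper bound. It requires every over-age visit to be missed and 30-80% of episodes to be found passively, and the protocol gives neither figure. If one in ten over-age visits is missed, the cut is 1-3%.

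The outcome exposed is the clinical-disease part of the age-incidence association, which could be modestly distorted. The arm ratio is not biased, although a few lost episodes would cost some precision. Infection endpoints from scheduled finger-prick samples do not depend on the age screen.

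**What to change.** In section 6.1.7, replace the age screen with an instruction that health-centre staff check every presenting child for the study sticker or study ID, or against the participant list, irrespective of current age. In section 6.1.9.1, name Albinama, with the surrounding aid posts, as the centre whose staff are briefed on the sticker.

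This costs two sentences of protocol wording and one staff briefing, with no extra staff, visits or samples. Once participants are identified regardless of age, the loss from ageing is zero. It has to be done prospectively, because a smear that was never taken cannot be recovered at analysis.
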